## PROBLEM STATEMENT

Family plays a vital role in the care of persons with Parkinson's disease. Due to the nature of the disease being chronic and progressive, with accompanying disabilities which worsen over time, care for this population is a significantly challenging task (van de Marck et al. 2009). The caregivers often experience long-term emotional and physical burden across all stages of the patient’s disease, which eventually threatens their well-being and quality of life. These, in return may reduce the quality of care given to the patient they cared for and consequently, affect the patient’s functional level and general health (Jenkinson et al. 2012). Therefore, caregivers’ wellbeing deserves attention in minimizing these consequences. To address these concerns, education and training to the family of persons with PD is important to equip them with adequate knowledge and care skills particularly as the disease progresses (Gultekin et al. 2017). Structured and comprehensive training programs would also enable the family to be better prepared for their role as caregivers and minimize emotional and physical burden, and these may result in improved QoL of the persons with PD and the caregivers. This is conceptualized in a framework as attached in appendix 1.

Currently, a few family education programs for people with PD are available as documented in the studies (Hellqivst et al. 2020; Bagheri et al. 2019; Navratha Sanche et al. 2019; Kessler & Liddy, 2017; Chaplin, Hazan & Wilson, 2015; A’ Campo et al. 2010; Guo et al. 2009; Lewis et al. 2009). However, the available programs are not comprehensive and focus mainly on knowledge regarding PD and its care, without the inclusion of care skills training. The programs have also not been evaluated for clinical effectiveness of variables such as functions and mobility plus the programs' sustainability and cost effectiveness remains questionable due to lack of follow up data. Due to these, more research that looks into developing and testing family training programs are needed.

In Malaysia, no research data is found to date on any structured family training program and its benefits on persons with PD. Available programs which are published in overseas studies, other than being less comprehensive, may not be suitable to be used in Malaysia due to the differences in care settings and organization of family life. A few local studies involving caregivers of the PD population reported significant perceived burden which was multi-factorial. However, no specific evidence-based program has been developed until now to overcome these caregivers' burden. Owing to the increase in the prevalence of PD in Malaysia as a result of population ageing, and the care burden that it heightened, it is warranted that an effective training program is to be developed and utilized towards enhancing the well-being of the person with PD and their family caregivers in this country. It is also emphasized in a recent study (Lidstone, Bayley & Lang, 2020) on the difficulty to evaluate the structure and efficacy of care models as these are not effectively reflected in clinical trial.

## NOVELTY AND RESEARCH SIGNIFICANCE

Structured, comprehensive family-training module has not been developed for persons with PD in Malaysia, and thus will be valuable for the local PD population and their family caregivers. This study will augment knowledge into the existing literature related to PD management and have implications on PD management of PD as both the persons with PD and their family caregivers are well prepared from Stage I or II of the disease. PD is a progressive disease, thus the home based clinical management is more apt for a smoother transition to palliative care later. Family assisted care training is crucial in PD as there is a shift of care from institution to community. There is no such study in Malaysia till date evaluating the effectiveness of family-assisted care training in persons with PD at home-based setting and therefore this study will provide crucial information on the feasibility information and the effectiveness. The evaluation of cost- effectiveness of training family as caregivers to implement care for patients with PD has not been attempted to date. Considering that PD is a chronic condition that requires long term care, evaluation of clinical efficacy as well as costs of a training program for caregivers are important to help reduce the disease burden. Caregiver burden has proven to reduce the quality of care provided to patients thus affecting the patient’s health and caregivers’ ability to provide care determines institutional placement. Therefore, development of this module which may be effective in improving function and QoL of PD persons through family assisted care. Further, providing rehabilitation from home is cost effective than institutionalization. It is important to train caregivers as Kalra and colleagues (2004) reported that training caregivers reduces burden and cost while improving outcomes for both patient and carers.

Table 1 Literature Review Matrix

| No. | Author and year | Aim | Methods | Intervention | Results and conclusion |
| --- | --- | --- | --- | --- | --- |
| 1. | Hellqivst et al. 2020 | To assess the outcomes of the Swedish  National Parkinson School (NPS) | Design: A quasi experimental study  Sample: 91 persons with PD patients and 55 family caregivers.  Outcome measures:   - Health status: PDQ-8 - Health valuation: EQ-5D - Health education impact: HeiQ - Life satisfaction: LiSat- 11 - Fatigue: PFS-16 - Caregiver burden: ZBI | - Programme based on principles of cognitive behavioral therapy and was developed based on the PEPP. - NPS includes the promotion of awareness of thoughts, feelings, and actions in relation to the impact of disease on daily life. - NPS also introduces techniques of self-monitoring in order to deliver the knowledge and tools in managing PD. | - Persons with PD reported improved health as indicated by both PDQ-8 (*p* = 0*.*028) and EQ5D (*p* = 0*.*023) scores following enrollment into NPS. - Improvements were also observed in the constructive attitudes and approaches (*P=* 0*.*003) and skill and technique acquisition (*P* < 0*.*001) of the HeiQ. |
| 2. | Lyons et al. 2020 | To explore the health benefits, self- management behaviors, illness communication  for partners in existing community-based self-management workshop for PD | Design: Quasi experimental  Sample: intervention group and control group consist of persons with PD and their caregiver (N = 39)  Outcome measure:   1. SF-36 2. CES-D 3. MCSI 4. Evaluation questionnaire CDSMP- Curriculum 5. Active engagement und protective buffering (VAS Scale) | Strive to thrive: Self-Management for Parkinson’s Disease   1. Self-management skills like monitoring, taking action, problem- solving, decision-making and evaluating results 2. Exercises (not further described), relaxation techniques 3. Six weeks of Chronic Disease Self-Management Program plus one week based on PD-specific content in group intervention format. | Preliminary data (*n* = 39 couples) reported couples in the intervention group had better engagement in mental relaxation techniques at 7 weeks compared to control condition.  Small effects were observed for increases in aerobic activity and mental relaxation for persons with PD, increases in strength-based tasks and self-efficacy for partners, declines in depressive symptoms for partners, and reduction in protective buffering for both adults with PD and their respective couples. |

| 3. | Bagheri et al. 2019 | This study  investigated the effect of a family- centered empowerment model on the burden of care among the  caregivers of the elderly with PD. | Design: RCT  Sample: 60 Caregivers and elderly with PD  Outcome measure: ZBI | Family-centered empowerment model consisted of four steps: Step 1: perceived threat  Step 2: problem-solving  Step 3: Educational participation Step 4: Evaluation  Intervention details: Three 10- persons groups in four- 45 minute sessions 2 days a week for 2 weeks. | Reduction in caregiving burden and improvement in the role of caregivers are observed.  Recommended to implement family- centered empowerment programs for the caregivers of persons with chronic diseases. |
| --- | --- | --- | --- | --- | --- |
| 4. | Navratha Sanche et al. 2019 | To evaluate the effects of a psychoeducational intervention compared with an education programme to  strengthen QoL, psychosocial adjustment, plus coping in people with PD and their caregivers | Design: Quasi Experimental Study  Sample: A total of 140 people with PD and 127 informal caregivers  Outcome measure: PDQ- 39, SQLC, PAIS-SR, The BRIEF COPE Scale. | The experimental group: nine week psychoeducational intervention  Control group: five week education programme. | Significant differences are observed between experimental and control groups for coping skills of patients and caregiver’s psychosocial adjustments.  Patients’ QOL and coping skills improved while the caregiver's coping skill and psychosocial adjustments improved following the intervention. |

| 5. | Kessler & Liddy, 2017 | To identify the characteristics of self-management programs for persons with PD and the evidence for their effectiveness. | Design: integrative literature review  Sample: Eighteen intervention studies. | 11 interventions were group based withy 1 and half hours per week for six to eight weeks delivered in person.  7 interventions were delivered on an individual basis, despite majority provided face to face, 2 intervention were delivered virtually.  Of the 18 interventions included in the study, only 16 were designed specifically for PD persons while remaining generally offered to persons diagnosed with chronic neurological disease.  Out of 18 interventions, only 4 interventions included caregivers or family members.  Key components of self-management support are education, problem- solving and goal setting. | |
| --- | --- | --- | --- | --- | --- |
| 6. | Chaplin, Hazan & Wilson, 2015 | To evaluate the Hertfordshire Neurological Services Self- Management Programme | Design: Program Evaluation survey post intervention  Sample: Stroke, PD, Multiple Sclerosis  Outcome measures: N/A | Intervention consist of following:  Module 1 – ‘What is self- management: pros and cons’ (all conditions, for service users and carers),  Module 2 – ‘Living Well’ (all conditions, for service users only)  Module 3 – Condition-specific information (for service users only). | Participant’s states expectations met from the modules.  Discussions and hearing other’s experiences was beneficial outcome of the course.  Suggestions to involve the caregiver in all modules |

| 7. | A’ Campo et al. 2010 | To evaluate the Effectiveness of the PEPP | Design: RCT  Sample: 65 PD patients and 47 caregivers  Outcome Measure:  The impact of psychosocial problems: BELA-P-k and BELA-A-k.  QoL patients: PDQ-39.  QoL caregivers: EQ-5D Depression: SDS. | PEPP is a standardized psychosocial intervention. The intervention consisted of eight weekly sessions of 90-minute duration.  8 sessions of PPEP; information, self-monitoring, health promotion, stress management, management of anxiety and depression + caregiver challenges, social competence, social support, evaluation | A significant effect for the caregivers on psychosocial problems & need help was observed and a trend for significance for patients’ QoL.  Persons with PD and caregivers’ mood improved significantly after each session. |
| --- | --- | --- | --- | --- | --- |
| 8. | A’ Campo et al. 2010  (2) | To undertake a formative evaluation of a standardized psychosocial education program for persons with PD and their respective caregivers | Design: Formative  evaluation of an experimental study  Sample: 17 caregivers and 151 PD patients participated in the 8-week program in separate groups.  Outcome measure: The impact of psychosocial problems: BELA-P-k and BELA-A-k.  QoL patients: PDQ-39.  QoL caregivers: EQ-5D Depression: SDS | Similar to above.  The program consisted of eight weekly sessions of ninety minutes. Groups consisted of 4–7 participants. | The program was feasible to run in the different countries. |

| 9. | Guo et al. 2009 | To evaluate the effect of a group education program with personal rehabilitation for persons with PD | Design: RCT with a pre- test/post-test quasi- experimental design.  Sample: 44 patients with PD Outcome measure:  PDQ-39, UPDRS, SEADL,  SDS, PMS, CMS. | 45 minutes of interactive dialogue group lecture and followed by individualized and tailored rehabilitation 24 half-hour sessions over eight weeks for the intervention group | Significant improvement observed following 8 weeks intervention for the health-related quality of life (HRQOL) (p<0.001).  PD persons and their caregivers in experimental group also reported their mood elevations following the program. |
| --- | --- | --- | --- | --- | --- |
| 10. | Lewis et al. 2009 | To evaluate the effect of the Stress- Busting Program (SBP) for family caregivers. | Design: RCT  Sample: A total of 209 caregivers of ADRD patients  Outcome Measure: QoL for caregivers was determined using a variety of questionnaires that assess mental, social, and emotional health. | Phase 1, 2, and 3 of the Stress Busting Program:  Phase 1 of SBP: Simple relaxation strategies.  Phase 2 of SBP involved multicomponent program for caregivers of patients with ADRD. Caregivers are given a handbook, a relaxation/meditation CD, and a resource book for caregivers.  Phase 3: This program is adapted to PD caregivers | Caregivers’ experiences significant decrease in perceived stress, depression, burden. They also reported improved general health, social function, and mental health scores. |

Note: Parkinson's disease Questionnaire (PDQ-8), EQ-5D (EuroQoL-5 Dimensions), The Health Education Impact Questionnaire (Hei Q), Life satisfaction: LiSat-11 (Life Satisfaction Questionnaire-11), Fatigue: PFS-16 (Parkinson Fatigue Scale), Caregiver burden: ZBI-22 (Zarith Burden Interview-22), Curriculum evaluation: Chronic Disease Self-Management Program (CDSMP), Center for Epidemiologic Studies Depression Scale (CES-D), The Modified Caregiver Strain Index (MCSI), Visual Analog Scale (VAS), Parkinson's disease Questionnaire -39 (PDQ-39), The Scale of Quality of Life of Caregivers (SQLC), The Psychosocial Adjustment to Illness Scale (PAIS-SR), Patient Education Program Parkinson (PEPP), Self- rating Depression Scale (SDS), Belastungsfragebogen Parkinson Kurzversion (BELA-P-k), Belastungsfragebogen Parkinson Angehörige Kurzversion (BELA-A-k), Unified Parkinson Disease Rating Scale (UPDRS), Schwab and England Activities of Daily Living (SEADL), Global patient’s mood status (PMS), Caregiver’s mood status (CMS), Alzheimer's Disease Related Dementias (ADRD).

## RESEARCH QUESTIONS

1. What are the caregiver’s perception and needs on current education and training in the development of family caregiver-training program for managing persons with PD?
2. What is the level of physical functioning and QoL among persons with PD in Malaysia?
3. How valid and reliable is the family caregiver-training program for persons with PD?
4. Is the family caregiver-training module feasible and well accepted by the people with PD and their family caregivers?
5. What is the difference between pre and post score of functions, mobility and QoL of persons with PD who receive a structured, multi-component family caregiver-training program when compared to those receiving the usual intervention?
6. What is the difference between pre and post score of knowledge, burden and QoL of family caregivers who receive a structured, multi-component family caregiver-training program when compared to those receiving the usual intervention?
7. How cost effective is the family caregiver-training program for persons with PD and their family caregiver?
8. How sustainable is the family caregiver-training program for persons with PD in terms of retention of effect, compliance and number of dropouts?

## OBJECTIVES

- 1. **General Objectives**

To develop and validate a structured multi-component training module plus establish its feasibility, acceptance, clinical effects, cost effectiveness and sustainability for family caregivers of persons with PD.

## Specific Objectives

1. To explore the caregiver perception and needs related to education and training in the caregiving of persons with PD.
2. To determine the level of physical functioning and QoL among persons with PD in Malaysia.
3. To design and validate a structured multi-component family-training program and determine its reliability.
4. To develop the structured multi-component family-training program and determine its feasibility and acceptance.
5. To compare the pre and post score of functions, mobility and QoL between persons with PD receiving the structured multi-component family-training program and usual intervention.
6. To compare the pre and post score knowledge, QoL and burden between family members of persons with PD receiving the structured multi-component family- training program and a usual intervention.
7. To evaluate the cost effectiveness of the structured multi-component family-training program and control group.
8. To determine the sustainability of the structured multi-component family-training program among the family of persons with PD.

## HYPOTHESIS

- 1. **Null Hypothesis**

The structured multi-component family-training program is not more effective clinically and by cost, when compared with a usual intervention in improving functions, functional mobility and QoL of persons with PD, carer knowledge, carer QoL and burden among family members of PD when compared to the usual intervention. The family-training program is not sustainable and not well accepted by family and people with PD.

## Alternate Hypothesis

The structured multi-component family-training program is more clinical and cost-effective than usual intervention in improving functional mobility and QoL of persons with PD, carer knowledge, carer QoL and burden among family members of PD when compared to the usual intervention. The family-training program is sustainable and well accepted by family and people with PD.

## METHODOLOGY

- 1. **Overall Design, Time Scale and Venue**

This study utilizes instructional design based on quantitative and qualitative research approaches. ADDIE model will be used in developing the family caregiver-training program,

which involves the process of analysis, design, development, implementation and evaluation (ADDIE) of the program. This study consists of Phase I, II and III corresponding to the all five phases of ADDIE model as shown in Figure 1. This study encompasses needs analysis, FGD, pilot and a full scale single blinded randomized controlled trial (RCT) with an addition of cost- effectiveness analysis. This study will be conducted at the Universiti Kebangsaan Malaysia Medical Centre (UKMMC) in collaboration with the Malaysian Parkinson’s Disease Association (MPDA). The study duration will be from April 2022 to October 2024.

1.
[figure not shown]
Literature Review
2. FGD
3. Analysis of function and QoL
   1. Early draft of Family Caregiver- Training Program
      1. Module Development
      2. Content Validation
      3. Pilot RCT
         1. Assessor blinded RCT

Figure 1 Overall design of the study based on ADDIE model

## PHASE I

Phase I of the study is the analysis phase of ADDIE model. Phase 1 of the study comprises of literature review, needs analysis of physical functioning and QoL of persons with PD and a FGD to aid in the design and development of family caregiver-training module. Generally, according to Muruganantham, (2015), analysis phase of ADDIE model comprise of needs assessment of the family caregiver-training program, problem identification of PD persons and their caregiver which is crucial to be addressed in the module plus goals and task analysis which includes determining solutions.

## Needs analysis of physical functioning and QoL of persons with PD

1. **Study design**

Needs analysis of physical functioning and QoL of persons with PD will utilize quantitative approach using cross sectional study design.

## Target population

Persons with PD in stage I and II.

## Sample population

Persons with PD in stage I and II, registered with the MPDA or referred to the Medical Rehabilitation Services Department of UKMMC.

## Inclusion and exclusion criteria of participants

Table 2 Eligibility criteria of participants for needs analysis

| **Inclusion criteria** | **Exclusion criteria** |
| --- | --- |
| 1. 50-75 years old 2. Stage I and II of Parkinson’s disease based on HY scale 3. Availability of family caregivers. | 1. Impaired physical function due to other conditions such as a recent fracture within the past 6 months, severe arthritis or other neurological disease such as peripheral neuropathy. 2. Have medical illness limiting participation in exercise, such as unstable angina and   uncontrolled hypertension. |

Hoehn and Yahr scale used for screening the eligibility of participants (persons with PD) are attached in Appendix 2.

## Sampling design and sample size calculation

A total of 196 participants will be recruited in this needs analysis from medical rehabilitation department from UKMMC or MPDA. The formula used to estimate sample size for this needs analysis will be according to Krejcie & Morgan (1970), using table for determining sample size from a given population that was derived from the formula (Krejcie & Morgan 1970). This formula was intended as the estimating population proportions at a specific probability and level of accuracy (Johnson & Shoulders 2019).

The formula used and its calculation was:

s = X^2^NP(1 – P) ÷ d^2^(N – 1) + X^2^P(1 – P)

s = (3.841)(400)(0.50)(1-0.50) ÷ (0.05)^2^ (400-1) + (3.841)(0.50)(1-0.50)

s = 196 participants

where, s is required sample size, X^2^ is the table value of chi-square for 1 degree of freedom at the desired confidence level (3.841), N is the population size, P is the population proportion (assumed to be .50 since this would provide the maximum sample size) and d is the degree of accuracy expressed as a proportion (.05).

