**2022**

1. **Background**

Parkinson’s disease (PD) is a progressive neurodegenerative disorder characterized by motor and non-motor features. The disease progression is contributed by progressive denervation and neuro-degeneration of various areas in the brain and peripheral nervous system (Kouli et al. 2018; Poewe & Mahlknect, 2009). Clinically, this is demonstrated by increasing severity of motor features for example postural instability and freezing of gait following the evolution of poor responsiveness towards PD medications. Further, a wide range of non-motor disorders may develop and contribute significantly to disability experienced by PD patients (Kouli et al. 2018). Parkinson's disease is the fastest developing of the neurological illnesses that are currently the major cause of disability in the world. As the population ages and life expectancy rises, so does the cost of healthcare. Statistics of people suffering from PD will continue to increase, as does the duration of condition, resulting in greater PD sufferers in advanced stages (Ray Dorsey et al. 2018).

The global prevalence of PD based on the 2016 statistics is 6.1 million (Ray Dorsey et al. 2018). The global burden of PD in the same year is high, reported as 3.2 million disability adjusted life years (DALYs) with greater than 200,000 reported deaths. The burden of PD worldwide is expected to rise due to increased life expectancy of the ageing population, which increases the necessity for extended care (Ray Dorsey et al. 2018). The prevalence of PD in Malaysia as of 2016 statistics are 19 586 with death count as 514. The age-standardized rate of DALYs in Malaysia is estimated as 9694 with 19.1% increase from 1991(Ray Dorsey et al. 2018). This data is alarming as it is further reinforced by a report published by the Department of Statistics Malaysia in 2018, the number of people with Parkinson's disease in Malaysia is anticipated to increase fivefold by 2040, from an estimated 20,000 to 120,000 (Hassandarvish, 2019).

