## (8) Statistical tool

Statistical Analysis Statistical Package for Social Sciences (SPSS) will be used and variables namely the level of physical functioning and QoL will be analyzed descriptively, presenting in mean and standard deviation.

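### The 5-point accuracy behind the Phase I sample of 196 holds only for a proportion in an unsourced population of 400, not for the Malaysian objective or for the mean scores reported

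*Protocol*

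**What the plan says.** All places are in the Protocol.

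- **Phase I, Sampling design and sample size calculation.** "A total of 196 participants will be recruited in this needs analysis". The size comes from the Krejcie and Morgan formula, with the substitution beginning "s = (3.841)(400)(0.50)(1-0.50". Among the other inputs, the accuracy is set by "d is the degree of accuracy expressed as a proportion (.05"); the multiplier for 95% confidence appears as "the table value of chi-square for 1 degree of freedom at the desired confidence level (3.841"); and the assumed proportion is explained by "P is the population proportion (assumed to be .50 since this would provide the maximum sample size"). N is labelled only as the size of the population. The same section says that the formula is meant for estimating population proportions.
- **Specific Objectives, objective 2.** "To determine the level of physical functioning and QoL among persons with PD in Malaysia". Research question 2 has the same scope.
- **Phase I, Target population and Sample population.** The target is people with PD in stage I or II, with no site limit. The sample population is those registered with the MPDA or referred to one UKMMC department. The size of that frame is not given.
- **Background.** "The prevalence of PD in Malaysia as of 2016 statistics are 19 586". No stage or age restriction is attached to the figure.
- **Phase I, (8) Statistical tool.** "variables namely the level of physical functioning and QoL will be analyzed descriptively, presenting in mean and standard deviation". The section with the needs-analysis flow chart lists frequency and percentage as well as mean and standard deviation.

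**The concern.** A finite-population formula earns its smaller sample by counting how much of the population has been observed. With 196 out of 400 that is 49%. The reduction is legitimate only for statements about those 400 people. The objective is worded for Malaysia, and nothing in the protocol links 400 to that population or to any other.

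The accuracy of 0.05 is also a distance between proportions. MDS-UPDRS Part II is a sum of 13 items scored 0 to 4, and PDQ-39 is built from Likert items. No cut-off is given that would turn either into a proportion. The accuracy that justifies 196 is therefore not the accuracy of the two results that the survey is meant to deliver.

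At stake is how the findings are described. A reader could take mean function and quality of life for Malaysian patients to be known to within 5 points of something, when that figure fits neither the population nor the statistic.

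**Working it through.** **Inputs.** From the sample size section: X² = 3.841, P = 0.50, d = 0.05, N = 400, n = 196. From the Background: 19,586 people with PD in Malaysia in 2016, all stages and ages. Other values of N below are assumptions, because the protocol does not give the number of eligible stage I–II patients.

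**1. Reproduce the protocol's figure.** The printed formula lacks brackets round its denominator. Read as intended:

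s = X²·N·P(1−P) / [d²(N−1) + X²·P(1−P)]

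- Numerator: 3.841 × 400 × 0.25 = 384.1
- Denominator: 0.0025 × 399 + 3.841 × 0.25 = 0.9975 + 0.96025 = 1.95775
- s = 384.1 / 1.95775 = 196.19

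The printed 196 is reproduced.

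**2. Accuracy for a proportion at n = 196.** Solving the same formula for d:

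d = √{ [X²·P(1−P)/n] × (N−n)/(N−1) } = √{ 0.0048992 × (N−196)/(N−1) }

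| N | Status | Half-width, percentage points |
|---|---|---|
| 400 | protocol input | 5.00 |
| 600 | assumed | 5.75 |
| 1,000 | assumed | 6.28 |
| 2,000 | assumed | 6.65 |
| 5,000 | assumed | 6.86 |
| 19,586 | protocol, all stages and ages | 6.96 |
| unlimited | limit | 7.00 |

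For example, N = 2,000 gives √(0.0048992 × 1,804/1,999) = √0.0044213 = 0.0665. Above about 2,000 the choice of N hardly matters.

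**3. Precision of a mean at n = 196.**

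- No finite-population correction: 1.96/√196 = 1.96/14 = 0.14 SD
- Inference to 400 people only: 0.14 × √(204/399) = 0.14 × 0.715 = 0.10 SD

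The sample size section gives no SD and no precision target for MDS-UPDRS Part II or PDQ-39, so these cannot be put into scale points from that calculation.

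Every half-width in steps 2 and 3 assumes simple random sampling.

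**The case against.** The best defence is that 400 is the combined MPDA and UKMMC frame from which participants are recruited. The calculation then matches the sample population, 5 points is correct for it, and all that is missing is one line of explanation. This may well be so, but the protocol does not say it. If it is so, objective 2 is still worded more widely than the frame, and the mismatch between proportion and mean remains.

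The flow-chart section does list percentages, so some proportions will be reported. That stands. No proportion of function or quality of life is defined, however, and the statistical section names mean and SD for exactly those two variables.

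A reader might infer something stronger: that the true national accuracy is 7 points, that the survey needs about 377 participants (N = 19,586 gives 376.73), or that its error bars will be too narrow. The documents do not support this, for three reasons.

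- The figure of 19,586 has no stage or age limit, while the survey takes Hoehn and Yahr stage I–II, age 50–75, with a family caregiver. With an assumed N of 2,000 the formula asks for 322.35, not 376.73.
- Recruitment is by WhatsApp from two registries, with no random selection from Malaysian patients described. No choice of N turns that into a national margin of error.
- The analysis is descriptive. No confidence interval and no finite-population correction are planned, so no error bar is wrong as written.

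**Conclusion.** The point holds in a limited form. The calculation of 196 is arithmetically correct. Its 5-point accuracy is valid only for a proportion in a population of 400 that the protocol does not identify. For a much larger target population the nominal figure at n = 196 is 6.6 to 7.0 points, for assumed N from 2,000 upward. It does not apply to the mean scores, whose nominal 95% half-width is 0.14 SD, or 0.10 SD for a 400-person frame.

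The importance is minor. No hypothesis test or decision rule depends on the 5 points. The sections on the focus group and on module design name the focus-group findings and the literature review as the basis for the module. The size and power of the Phase III trial do not depend on this calculation.

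**What to change.** Keep n = 196 and change the wording of the sample size section and of objective 2.

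1. State what the 400 counts and where it comes from. If it is the MPDA and UKMMC frame, say that the 5-point accuracy applies to proportions in that frame, and limit the inference of objective 2 (and research question 2) to it.
2. Replace or supplement the 5 points with the precision of the statistics reported: a nominal 95% half-width of 0.14 SD for mean MDS-UPDRS Part II and PDQ-39, or 0.10 SD where inference is to the 400-person frame only. State the simple-random-sampling assumption beside it.
3. Do not print a margin of error for Malaysia.

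The cost is a few sentences and a narrower stated scope. No extra participants are needed.
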